### 1.4 Exploratory Objectives

1.4.1 To assess the relationship of antifungal drug susceptibility of cryptococcal isolates to fluconazole and microbiological and clinical outcomes.

1.4.2 To assess the pharmacology [pharmacokinetics (PK), pharmacodynamics (PD)], and toxicity of high-dose fluconazole and, if samples are available, relationships with concomitant RIF and/or efavirenz (EFV) (see section 10.1 for specific pharmacology objectives].

1.4.3 To evaluate a lateral flow cryptococcal antigen (LFCrAg) detection assay using urine, serum, plasma, and CSF samples from participants with confirmed CM.

## 2.0 INTRODUCTION

### 2.1 Background

Cryptococcal meningitis (CM) is the most common central nervous system (CNS) complication of AIDS worldwide and accounts for up to 1/3 of all deaths from AIDS in many parts of the developing world [Pitisuttithum, 2001; Mwaba, 2001; Ford, 2000; Gangaidzo, 1999]. With the dissemination of antiretroviral therapy (ART), which provides the possibility of long-term survival after diagnosis of CM, development of practical CM therapy has become a high priority. Treatment of CM is problematic in locations with limited resources: treatment with an ampho B-based regimen requires maintaining intravenous (IV) access, monitoring and treating acute infusion reactions, and monitoring of common, cumulative treatment-limiting toxicities (TLTs) such as renal dysfunction and electrolyte imbalance (particularly low K+ and Mg++). In addition, the price of ampho B is often prohibitive. Thus, costs of ampho B, its administration, and the requisite safety monitoring often preclude its use in resource-limited settings, leaving patients untreated for CM or treated with inadequately effective low-dose regimens of fluconazole only.

Because fluconazole is widely available, inexpensive, can be given orally, has a demonstrated safety profile over a broad range of doses, and has proven activity against *Cryptococcus neoformans*, the use of fluconazole to treat CM is quite appealing. Even in developed countries, the use of high-dose fluconazole as an alternative to ampho B-based regimens for severe cases of CM would also be desirable. Elimination of the requirement for the two weeks of daily IV infusions of ampho B that is currently recommended for induction therapy of CM would likely reduce the number and degree of TLTs. In addition, the use of high-dose fluconazole alone would prove cheaper and far more convenient.

At the most common fluconazole dose of 200-400 mg/day, however, overall clinical success is expected in only 34 to 42% of patients [Larsen, 1990; Saag, 1992]. When fluconazole at 400 mg/day is combined with flucytosine, overall success is improved [Larsen, 1994] and is comparable to that of ampho B followed by fluconazole [van der Horst, 1997]. The median cost of ampho B is $6.73 (U.S.) per 50-mg vial; fluconazole is $0.20 per 200-mg capsule and $0.82 per 200-mg vial [World Health Organization (WHO) drug pricing information 2004]. Thus, fluconazole at 2000 mg/day (the highest dose proposed in this study) is comparable in price to ampho B, even if some doses must be provided by IV infusion.

2.1.1 Fluconazole

Fluconazole is a synthetic triazole antifungal agent. It is a highly selective inhibitor of fungal cytochrome P450-dependent sterol C-14 alpha-demethylation. The subsequent loss of normal sterols correlates with the accumulation of 14 alpha-methyl sterols in fungi and may be responsible for the fungistatic activity of fluconazole.

The pharmacology of fluconazole has been well studied only at doses of 50-400 mg per day. It is well absorbed orally (~ 90%), with peak plasma concentrations reached within 1-3 hours after dosing, and is not affected by food. Peak plasma concentrations at steady state on daily dosing are usually about twice those at trough. Fluconazole is minimally protein bound, widely distributed in body water with an apparent volume of 0.7 L/kg, and 80% is excreted unchanged in the urine with a half-life of 25-30 hours. About 11% is excreted in the urine as the glucuronide and N-oxide metabolites, which are both inactive and probably come from metabolism in the liver by cytochrome P450 3A4 enzymes. Renal insufficiency markedly prolongs the excretion of the drug.

Steady state is reached in plasma in 5-10 days on daily dosing, with steady state plasma concentrations of 4.6 and 9 mg/L after 200 and 400 mg doses, respectively. Cerebrospinal fluid (CSF) levels are 50-90% of those in serum [Foulds, 1988]. Over the range of 100–400 mg orally, the variation of fluconazole maximum plasma concentration (Cmax) and area under the concentration–time curve (AUC) are proportional to the administered dose. The elimination half-life and the time of Cmax also remain constant in this dosing range. This indicates the linearity of the pharmacokinetics (PK) of fluconazole for oral doses of 50-400 mg [Tett, 1995; data on file with Pfizer].

Adrenal insufficiency (AI) could be an issue in A5225 participants for three reasons: 1) AI is considered an uncommon complication of destruction of the glands by opportunistic infections (especially cytomegalovirus infection), neoplasms, or other conditions complicating advanced AIDS. Massive damage is required to induce AI since adequate function can be maintained by only 10% of the glands; 2) AI associated with critical illness is caused by both failure of corticosteroid production and tissue corticosteroid resistance and is characterized by exaggerated and protracted pro-inflammatory responses; 3) AI may be induced by high dose fluconazole possibly by toxicity to the p-450 systems of adrenal cells, similar to that recognized for ketoconazole, but induced by ketoconazole at concentrations 100-fold less than those required for fluconazole in a rat model.

Two small studies have prospectively evaluated the prevalence of AI in HIV patients. In 25 well (n=9) or critically ill (n=16) patients, 5 (19%) had AI by criteria of stress cortisol < 18 [Prasanthai 2007]. Fourteen of 28 (50%) critically ill patients were diagnosed with AI in another study by these same criteria [Marik 2002].

Four of the 854 (prevalence of 0.47% or 1/200) patients who were seen over 9 years in Taiwan were found to have AI, three by criteria of low cortisol and/or high ACTH levels or inadequate responses to ACTH stimulation. The fourth patient was on 800 mg of fluconazole for 68 days and was suspected, but not proven, to have AI, based on symptoms and other non-specific laboratory values which resolved after discontinuation of fluconazole. This low rate is consistent with the large reserve of the gland [[Huang](http://www.ncbi.nlm.nih.gov/sites/entrez?Db=pubmed&Cmd=Search&Term="Huang YW"%5BAuthor%5D&itool=EntrezSystem2.PEntrez.Pubmed.Pubmed_ResultsPanel.Pubmed_DiscoveryPanel.Pubmed_RVAbstractPlus) 2004].

To date, QT interval prolongation has been demonstrated with azole antifungal agents, including ketoconazole, itraconazole and fluconazole [Khazan 2002, Roden 2004, Gandhi 2003, Tholakanahalli 2001, Pham 2006, Esch 2008, Gupta 2007, Kannankeril 2007]. Post-marketing surveillance reports have documented rare cases of QT prolongation and torsade de pointes in patients receiving fluconazole, generally in seriously ill patients with multiple confounding risk factors [Diflucan 2011 package insert, Wassmann 1999, Dorsey 2000]. Azoles may cause prolongation of the QT interval either directly or by inhibiting the hepatic metabolism of other QT-prolonging agents. Ketoconazole is known to block the human ether-a-go-go-related gene (hERG) product, and thereby inhibit the potassium Ikr current in the heart [Takemasa 2008]. Whether fluconazole also inhibits hERG is currently unknown. However, all azoles inhibit cytochrome 3A4 to some extent, although fluconazole is a relatively weak inhibitor of this enzyme. The ICH E14 Guidance Document for Industry helps in assessing clinical evaluation of QT/QTc interval prolongation and proarrhythmic potential for non-antiarrhythmic drugs [International Conference on Harmonisation, 2005].

Toxicity of fluconazole is infrequent at low doses, and that observed at high doses in a phase II clinical trial conducted in the U.S. by the California Collaborative Treatment Group (CCTG) is discussed below. Patterns of abnormal aspartate aminotransferase (AST), alanine aminotransferase (ALT), alkaline phosphatase, gamma-glutamyl transferase (GGT), and bilirubin values did not suggest that fluconazole treatment was associated with an increased risk for hepatotoxicity, although a marked elevation of some of theses enzymes occurred in approximately 1% of patients.

The CCTG trial demonstrated improved clinical outcomes with increasing doses of fluconazole [Milefchik, 2008]. The composite 10-week overall response rates (success defined as alive and CSF culture negative) for fluconazole with and without flucytosine are shown in Figure 1. Of note, fluconazole alone for 10 weeks at the highest doses (1600 mg and 2000 mg/day) had clinical success rates over 60%, comparable to the overall success seen when ampho B is used for 2 weeks followed by fluconazole at 400 mg daily. As the CCTG trial was small and principally designed to assess the safety of higher dose fluconazole with and without flucytosine, a larger phase II trial is needed to confirm these findings in multiple settings and to assess the potential of an all oral treatment regimen to supplant the standard ampho B-based regimen.

Higher doses of fluconazole have been safely employed in the treatment of CM [Haubrich 1994], histoplasmosis [McKinsey 1996], candidemia [Rex 2003], and coccidioidomycosis [Galgiani 1993]. When higher dose fluconazole (up to 2000 mg daily) has been used alone, few serious toxic side effects have been observed (granulocytopenia 4%, and increased liver enzyme test 2%; see Table 2-1).

Table 2-1: Summary of Toxicity Events, CCTG Trial

| Toxicity | Fluconazole alone  N (%) | Fluconazole plus Flucytosine  N (%) |
| --- | --- | --- |
| Sweating | 6 (12%) | 6 (15%) |
| Tachycardia | 7 (14%) | 7 (18%) |
| Abdominal pain | 8 (16%) | 5 (12%) |
| Constipation | 8 (16%) | 6 (15%) |
| Diarrhea | 10 (20%) | 7 (18%) |
| Nausea | 29 (59%) | 23 (57%) |
| Vomiting | 27 (55%) | 24 (60%) |
| Weight loss | 9 (18%) | 8 (20%) |
| Anemia | 7 (14%) | 1 (3%) |
| Granulocytopenia (< 500) | 2 (4%) | 7 (18%) |
| Thrombocytopenia (<50K) | 0 | 3 (7%) |
| Hepatic enzyme increase (1.5x) | 1 (2%) | 3 (7%) |
| Alopecia | 6 (12%) | 4 (10%) |
| Dry skin | 9 (18%) | 13 (32%) |
| Increased skin pigmentation | 1 (2%) | 1 (3%) |
| Decreased hearing | 3 (6%) | 5 (12%) |

When higher dose fluconazole has been combined with flucytosine, the expected hematological side effects (granulocytopenia 18% and thrombocytopenia 7%) were easily detected by regular monitoring. In the CCTG trial, doses of fluconazole at 800, 1200, 1600, and 2000 mg with and without flucytosine were evaluated. Four dosing cohorts were employed, with participants randomly allocated between treatment cells. The baseline demographics of that study population are presented in Table 2-2.

Cohort 1: fluconazole @ 800 mg with/without flucytosine and 1200 mg of fluconazole alone.

Cohort 2: fluconazole @ 1200 mg with/without flucytosine and 1600 mg fluconazole alone.

Cohort 3: fluconazole @ 1600 mg with or without flucytosine.

Cohort 4: fluconazole @ 2000 mg with or without flucytosine.

A trial of fluconazole at 10 mg/kg/day (equivalent to about 800 mg) for candidemia noted elevations in liver enzymes in 14 of 30 patients, but clear attribution to fluconazole toxicity in this setting is not possible [Graninger 1993].

Adverse events related to fluconazole at 800 mg daily were reported by 48% of patients in a multicenter, randomized, open-label study to determine the efficacy and safety of two different daily doses of fluconazole (400 and 800 mg) in the treatment of non-life-threatening blastomycosis. One patient of 20 who received 800 mg daily presented a moderate elevation of liver transaminase level [Pappas 1997].

Another trial of fluconazole was conducted in cancer patients with presumed or proven mold infection. Groups of patients received fluconazole at four dosages (800, 1200, 1600, or 2000 mg/day). Adverse events, plasma levels, and clinical response were examined. Eight of 39 evaluable patients had elevated liver function test results that were either possibly or probably related to fluconazole [Anaissie 1995].

In addition to these studies, a few published reports in the past 20 years have shown severe fluconazole-induced hepatotoxicity despite treatment of cocciciodomycosis and blastomycosis at doses of 800 mg/day [[Crerar-Gilbert](http://www.ncbi.nlm.nih.gov/sites/entrez?Db=pubmed&Cmd=Search&Term="Crerar-Gilbert A"%5BAuthor%5D&itool=EntrezSystem2.PEntrez.Pubmed.Pubmed_ResultsPanel.Pubmed_DiscoveryPanel.Pubmed_RVAbstractPlus)  1999; [Jacobson 1994.]](http://www.ncbi.nlm.nih.gov/sites/entrez?Db=pubmed&Cmd=Search&Term="Jacobson MA"%5BAuthor%5D&itool=EntrezSystem2.PEntrez.Pubmed.Pubmed_ResultsPanel.Pubmed_DiscoveryPanel.Pubmed_RVAbstractPlus) For example, an 81-year old patient with renal impairment developed fulminant hepatic necrosis within 10 days of fluconazole 400 mg daily when his fluconazole serum level was 982 ug/mL (normal range 6-15 ug/mL) and without exposure to other potentially hepatotoxic drugs. These levels are clearly 10-fold higher than those expected and result from the effects of either renal failure or potentially from unrecognized dosing errors [Bronstein 1997].

Table 2-2: Demographic Information, CCTG Trial

In a recently published clinical study in Uganda, fungicidal activity was greater over two weeks in 30 participants treated with fluconazole at 1200 mg daily for 2 weeks than in 30 participants treated initially with fluconazole at 800 mg daily for 2 weeks [Longley 2008]. After two weeks, participants were followed on 400 mg per day for the next 8 weeks. There were no serious fluconazole dose-related toxicities in either dosing cohort and similar numbers survived in two cohorts.

Summary of Data from Cohort 1

The study’s first cohort (Cohort 1, 1200 mg daily fluconaozole or ampho B-based regimen) was opened to accrual on February 19, 2010. The ACTG A5225 Study Monitoring Committee (SMC) met by conference call on September 28, 2011, to review the A5225 Monitoring Plan and the SMC Report. After carefully reviewing the accrual, safety and efficacy data, the SMC concluded that no significant efficacy or safety concerns were identified. The SMC provided the following recommendations to the team:

1. Because of the low rate of dose-limiting toxicity (DLT) observed with study of 20 participants enrolled in Cohort 1 to date, it is very unlikely that an unacceptable DLT rate would be observed after completion of planned enrollment (5 additional participants) of Cohort 1. The SMC therefore recommends that Cohort 1 should be closed and enrollment of Cohort 2 should begin.

2. An additional ECG should be performed on or near study day 28.

3. When deciding whether or not an event should be considered a DLT and how to manage toxicities, the team should adhere to a strict interpretation of toxicity grades as defined in the DAIDS table. Specifically, both a ≥0.06 sec increase of the QTc above baseline and a QTc ≥0.50 sec should both be considered Grade 3 adverse events since both are criteria for Grade 3 prolonged QTc in the DAIDS adverse event grading table.

4. The SMC noted that azithromycin, which has been reported as a cause of prolonged QTc and torsades de pointes, is not listed among the precautionary medications in the protocol Manual of Operations. Azithromycin should be added to this list and the team should review this list periodically to ensure that it is complete and up to date.

5. The next SMC review should occur when enrollment of Cohort 2 is completed or in one year, whichever comes first.

Cohort 1 was closed to accrual on October 7, 2011, with a total of 29 participants enrolled. Cohort 2 opened to enrollment on October 7, 2011.

Drug-Drug Interactions

Fluconazole has been associated with many clinically important drug interactions. These interactions are mainly due to fluconazole’s inhibitory effects on CYP450 3A4 enzyme and, to a lesser extent, inhibition of 2C8, 2C9, and 2C19. Therefore, medications that are metabolized by CYP450 enzymes may have enhanced concentrations when given concomitantly with fluconazole. Additionally, 11% of fluconazole is metabolized by glucuronidation and oxidation (by P450 enzymes) to inactive metabolites, thereby allowing for effects on fluconazole concentrations by other medications that affect these metabolizing enzymes. Pertinent drug interactions related to this protocol are discussed below.

Nevirapine (NVP) is widely employed in the treatment of HIV in low resource settings and has been used widely in persons who have recovered from CM. Data on the safety of coadministration of fluconazole 200 mg daily with NVP are possibly conflicting as documented in two studies.

The safety and pharmacology of fluconazole 200 mg given with NVP 400 mg once daily was studied in an open-label, single-arm trial examining the PK parameters of fluconazole alone and in combination with NVP in 24 patients on a stable 3-nucleoside ART regimen [Manosuthi, 2007]. The majority of individuals were black (76%) and female (68% in the PK study, 71% in the safety study). Clearance of NVP was halved when fluconazole was added, resulting in an approximate doubling of NVP Cmin, Cmax, and AUC compared with historical data from Boehringer Ingelheim's studies. The high peak NVP levels (Cmax = 12.9ng/mL; range = 3.0-17.9) seen led to a surprisingly high incidence (25%) of liver toxicity, compared with historical data (2.5%). Nearly all (95%) of the NVP-related AEs occurred after full dosing (400mg daily) of NVP was instituted (day 39 of the study). During this phase, 25% (CI 7-43%) of patients developed serious hepatotoxicity, including 2 cases of clinical hepatitis and 6 cases of transient Grade 4 transaminase elevation. Three cases of rash were seen, 2 (8.3%) macular-papular, and 1 (4.2%) vesicular.

In a retrospective review of liver function by biochemical tests, 69 Thai patients (average weight 59 kg) taking NVP-based ART regimens and 200 mg of fluconazole daily were compared with 392 patients taking 400 mg fluconazole weekly and 225 taking no fluconazole with their ART [Geel, 2004]. No differences in biochemical hepatitis or ability to take the regimens were found.

Based on these data, coadministration of these two drugs is discouraged in A5225/HiFLAC. Furthermore, coadministration of NVP and fluconazole at fluconazole doses > 400 mg daily is prohibited in A5225/HiFLAC. While the decision regarding coadministration of NVP and fluconazole at fluconazole doses of ≤ 400 mg fluconazole daily is left to the discretion of the treating clinician, we strongly urge the institution of weekly monitoring of hepatic enzymes [Manosuthi 2007].

Limited data on the coadministration of fluconazole and EFV have demonstrated a small increase in EFV exposures with no change in fluconazole concentrations. Beginning at week 4, EFV may be used concomitantly with fluconazole without regard to fluconazole dose.

When zidovudine (ZDV) is administered at 200 mg every 8 hours concomitantly with 400 mg fluconazole daily, Cmax and AUC of ZDV were increased 84.2%, and 74.4%, respectively [Sahai 1994]. Therefore, caution should be used when coadministering these two drugs.

Limited data on the drug interaction between RIF and fluconazole demonstrate enhanced metabolism of concurrently administered fluconazole, thereby reducing the AUC of fluconazole by 23% [Apseloff 1991]. Therefore, the use of RIF is prohibited for A5225/HiFLAC study participants receiving 1200 mg daily fluconazole. RIF may be initiated after these participants have initiated the consolidation dose of 600 mg fluconazole daily (rather than 400 mg daily) or the maintenance dose of 200 mg daily fluconazole. Coadministration of fluconazole with RIF is permitted in the higher induction dose cohorts (1600 mg and 2000 mg daily), however, because the impact of any drug-drug interaction (i.e., the extent to which RIF will reduce fluconazole concentrations) is expected to be lessened at these doses. Medications that are prohibited from coadministration with fluconazole are listed in the A5225/HiFLAC Manual of Operations (MOPS) as are those that may be administered with caution.

Additional information can be obtained from the latest fluconazole package insert.

Considerations Regarding Participant Follow Up

Missing data elements, particularly those required to assess clinical outcomes, potentially confound interpretation of results. In a double-blind multicenter trial, patients with a first episode of AIDS-associated CM were randomly assigned to treatment with higher-dose ampho B (0.7mg/kg per day) with or without flucytosine (100 mg/kg per day) for 2 weeks, followed by8 weeks of treatment with itraconazole (400 mg per day)or fluconazole (400 mg per day). Treatment was consideredsuccessful if CSF cultures were negative at2 and 10 weeks or if the patient was clinically stable at 2 weeks and asymptomatic at 10 weeks [van der Horst 1997]. An example of distortions produced by missing data is found in the analysis of this trial. A missing CSF culture was deemed positive and the patient was assigned as failing study therapy (Table 2-3). This assumption may have significantly overestimated the incidence of failure. Thus, losses to follow up and failure to collect critical data have probably inflated incidence of failure in past studies and may obscure clinically meaningful differences in treatment outcomes in comparative studies. Therefore, we will attempt to ensure that sites are adequately prepared to conduct this trial and that necessary training is provided.

Table 2-3: Clinical Failure [van der Horst]

|  | Week 2 | | Week 10 | |
| --- | --- | --- | --- | --- |
| Treatment | AmB+5FC | AmB alone | fluconazole | itraconazole |
| Subjects | N= 202 | N= 179 | N= 151 | N= 155 |
| Success (CSF negative) | 122 (60%) | 91 (51%) | 109 (72%) | 93 (60%) |
| Failure | 80 (40%) | 88 (49%) | 42 (28%) | 62 (40%) |
| CSF culture positive | 47 (59%) | 55 (62%) | 3 (7%) | 8 (13%) |
| No CSF sample | 33 (41%) | 33 (38%) | 39 (93%) | 54 (87%) |

Before implementing A5225/HiFLAC, potential sites will be required to document their ability to initiate the study, enroll adequate numbers of participants, conduct clinical investigations according to good clinical practice, follow the protocol outline as specified, and complete the study procedures [lumbar punctures (LP) and CSF cultures]. During the conduct of the study, sites will be asked to periodically provide the team with documentation of their practices in response to issue-specific inquiries. Submission of a revised A5225/HiFLAC SIP may be required. Collaboration among ACTG international sites in this phase I/II clinical trial should prepare them for the larger phase III trial that will probably follow (see below).

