# GLOSSARY OF STUDY-SPECIFIC TERMS

##### 5FC 5-fluorocytosine

ampho B amphotericin B deoxycholate (in A5225/HiFLAC, the abbreviated name is being used for convenience and is not intended to represent an official name for the drug)

ampho B-based regimen in this study, a regimen that is either ampho B alone or ampho B in combination with 5-fluorocytosine **or fluconazole, according to local standard of care**

CCTG California Collaborative Treatment Group

CM cryptococcal meningitis

CNS central nervous system

CSF cerebrospinal fluid

DLT dose-limiting toxicity: interruption of an induction dose of study-provided fluconazole (i.e., 1200 mg, 1600 mg, or 2000 mg daily) for at least 3 consecutive days as the result of a fluconazole-related toxicity, where the discontinuation was initiated prior to day 14

ECG electrocardiogram

EFV efavirenz

hERG human ether-a-go-go-related gene

HiFLAC High-Dose Fluconazole for Treatment in AIDS-Associated Cryptococcal Meningitis, acronym for A5225

IRIS immune reconstitution inflammatory syndrome

LFCrAg lateral flow cryptococcal antigen (assay)

LP lumbar puncture

MOPS manual of operations

MTD maximum tolerated dose, defined for A5225/HiFLAC as the highest dose of fluconazole that can be safely used [i.e., a dose that results in a ≤ 25% rate of fluconazole dose-limiting toxicity (DLT)].

PML progressive multifocal leukoencephalitis

SIP site implementation plan

SMC study monitoring committee

SoC standard of care

SoE schedule of events (protocol section 6.1)

TEN toxic epidermal necrolysis

TLT treatment-limiting toxicity: a toxicity that results in discontinuation of ampho B-based treatment prior to day 14 and prior to receipt of a total of 8.4 mg/kg ampho B

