### 1.2 Primary Objectives

1.2.1 To assess the MTD of fluconazole by comparing the safety and tolerability of induction regimens of 1200, 1600, and 2000 mg/day.

1.2.2 To determine whether the safety and efficacy of high induction-dose fluconazole therapy support development of a phase II/III trial, and, if so, to select the most appropriate fluconazole dose regimen (based on safety and efficacy data from this study) to be evaluated in that trial.

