6.3.12 ECG

Resting ECG results, including heart rate and measured QT interval, must be recorded as indicated in the SoE, sections 6.1. The QT interval should ideally be taken from limb lead II. See section 7.2 for clinical management directions for participants with prolonged QT interval on study. Note that when recording QT interval at visits after entry, the site is responsible for documenting any change relative to the baseline value.

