### Fluconazole-Induced Prolongation in QT Interval

The QT interval has an inverse relationship to heart rate; the measured QT intervals are generally corrected for heart rate in order to determine whether they are prolonged relative to baseline. The site is responsible for documenting any change relative to the baseline value.

Various correction formulae have been suggested, of which the Fridericia’s correction is most widely used. The correction factor used in this protocol is given below.

Fridericia’s correction: QTc = QT/RR0.33, or,

the QT interval divided by the cube root of the RR interval

Grade 1: Fluconazole should continue without interruption, at the discretion of the site investigator.

Grade 2: Fluconazole should continue without interruption, at the discretion of the site investigator. A repeat ECG should be considered 1 week later.

Grade 3: Fluconazole should be interrupted. If the Grade 3 QTc prolongation is considered to be most likely due to concomitant illness or medication, standard management, including discontinuation of the likely causative agent, should be undertaken. If the QTc prolongation resolves to Grade ≤ 1 within 3 days, the investigator should consider whether fluconazole can be re-started, as described in 7.1. If the QTc prolongation does not resolve to Grade ≤ 1 within 3 days, study-provided fluconazole should be discontinued and the participant referred to SoC.

Grade 4: Participants should permanently discontinue fluconazole.

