### 9.5 Analysis

9.5.1 Stage 1

Dose escalation is based on DLT and the decision rules as outlined above. As noted above, between-dose comparisons to select the fluconazole dose(s) to carry forward will largely be descriptive and not formally powered as all information will be factored into this decision.

9.5.2 Stage 2

In this pilot, we intend to combine the data over both Stages for the ampho B-based cohorts and for fluconazole doses that are tested in Stage 2. As noted above, only the confidence interval around the observed DLT rate in each dose will be adjusted for the dose escalation scheme. Analyses will employ appropriate methods such as Fisher’s exact test to compare dichotomous outcomes (e.g., Grades 3 and 4 events; CSF clearance before week 10) between doses or drugs, and t-tests or Wilcoxon tests to compare continuous covariates between two groups (or ANOVA or Kruskall-Wallis tests if three groups including ampho B). In the event all three fluconazole doses are evaluated in Stage 2, tests for trend such as ANCOVA, Cochran-Armitage and Jonckheere-Terpstra tests will be performed. Survival and other measures of time-to-event from study entry will be summarized with Kaplan-Meier estimates and, where appropriate, tested with log rank tests and possibly proportional hazards regression. The duration of the initial hospitalization will need to consider the duration of hospitalization preceding study entry. The focused neurological exam will be analyzed both on an item-by-item basis and also as a summary measure using methods such as mixed models analysis of variance or GEE that accommodate missing data and changing covariates.

The content and schedule of reports to be available to the core team, the SMC, and the full team will be detailed in the Study Monitoring Plan that will be developed prior to the opening of accrual to the study.

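### QTc comparisons of 1200 mg with the higher doses span a change in ECG schedule and grading instruction made as Cohort 1 closed

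*Protocol*

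**What the plan says.** Section 2.1.1 (Summary of Data from Cohort 1) gives the dates. Cohort 1, with 1200 mg or an ampho B-based regimen, opened on 19 February 2010. The monitoring committee met on 28 September 2011. Cohort 1 closed and Cohort 2 opened on 7 October 2011.

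Two of the committee's recommendations bear on QTc. The first is "An additional ECG should be performed on or near study day 28". The second, addressed to DLT decisions and toxicity management, is that "the team should adhere to a strict interpretation of toxicity grades as defined in the DAIDS table", and specifically that "both a ≥0.06 sec increase of the QTc above baseline and a QTc ≥0.50 sec should both be considered Grade 3 adverse events".

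The current schedules of events (6.1.2 and 6.1.3) place on-treatment ECGs at Day 4, Day 7 and week 4 for both fluconazole and ampho B participants. Section 6.3.12 states: "Resting ECG results, including heart rate and measured QT interval, must be recorded as indicated in the SoE".

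Objective 1.2.1 is to assess the MTD by "comparing the safety and tolerability of induction regimens of 1200, 1600, and 2000 mg/day". Outcome 9.2.1.1 (discontinuation with its precipitating adverse events) and outcome 9.2.2.5 (Grade 3 and 4 events, dose modifications, interruptions) carry no day-14 limit. Section 9.5.2 names Fisher's test, among others, for use "to compare dichotomous outcomes (e.g., Grades 3 and 4 events; CSF clearance before week 10) between doses or drugs". It also pools the ampho B cohorts over both stages.

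**The concern.** Only Cohort 1 received 1200 mg, so a change in how QTc is looked for and graded at the end of that cohort coincides with the step from 1200 mg to the higher doses. An all-visit count of Grade 3-4 QTc events would then set a dose probably observed mostly on Days 4 and 7 against doses observed at week 4 as well. Section 2.1.1 puts plasma steady state at 5 to 10 days of daily dosing, so Day 7 can fall before it and week 4 falls after it.

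If the two QTc criteria were not both being applied before the committee's advice, the grading difference would push the same way. At stake is the QTc part of the three-dose safety comparison: an apparent dose trend could arise partly from ascertainment.

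**Working it through.** **1. Who could have had the added ECG.** The week-4 window ends at day 31. A participant who started before about 28 August 2011 had left it before the meeting of 28 September. From 19 February 2010 to 28 August 2011 is 555 days; to closure on 7 October 2011 is 595 days. So about 93% of the accrual period (555/595) lies before that date. Enrolment by date is not given, so this supports 'most, probably' and no more. Two ECGs for those participants is inferred by removing the added one from the current schedule.

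**2. Which endpoints the added ECG can reach.** The Glossary limits a DLT to an interruption "where the discontinuation was initiated prior to day 14". A day-28 finding therefore adds nothing to the DLT count, the escalation rule, the MTD or the cardiac-DLT review trigger. It can reach Grade 3-4 events, and interruptions or discontinuations after day 14.

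**3. Which endpoints the grading can reach.** Section 7.2 says "Grade 3: Fluconazole should be interrupted". A Grade 3 reading on Day 4 or Day 7 can thus start an interruption before day 14, and at least three consecutive days of it is a DLT.

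**4. The plan's own figures.** Section 9.3.1 gives 88% for at least one cardiac DLT at a 10% rate: 1 − 0.90^20 = 0.878 (0.902 with 22 participants). Table 9-2 gives P(escalate) at a 10% DLT rate as .867 (N=20) and .828 (N=22). The sum over x = 0 to 3 of C(n,x)p^x(1−p)^(n−x) reproduces both.

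**5. Size of the schedule effect (illustration).** The protocol gives no QTc event rate. Assume a chance q of a Grade 3 reading per ECG, the same at every dose and independent between ECGs. The share with at least one such reading is 1 − (1−q)^k:

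| q | k = 2 | k = 3 | Ratio |
|---|---|---|---|
| 2% | 4.0% | 5.9% | 1.49 |
| 5% | 9.8% | 14.3% | 1.46 |
| 10% | 19.0% | 27.1% | 1.43 |

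With 22 participants per dose, the three-ECG dose shows strictly more affected participants with probability 47%, 59% and 68% at these values of q. Otherwise the counts tie or reverse.

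**6. Pooled ampho B.** Cohort 1B was planned at 8 of a target 48. At q = 5%, with 40 participants on three ECGs and 8 on two, the pooled share is (40 × 0.1426 + 8 × 0.0975)/48 = 13.5%, against 14.3% if all had three.

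**7. Size of the grading effect on DLT (illustration).** If strict grading added an assumed 2 or 5 percentage points to a 10% DLT rate, P(escalate) would fall from 0.867 to 0.787 or 0.648 (n=20), and from 0.828 to 0.733 or 0.575 (n=22). The documents do not show that any such addition occurred.

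**The case against.** **The formal comparison largely leaves out 1200 mg.** Section 9.5.2 covers ampho B and the fluconazole doses tested in Stage 2, and Table 2 lists 1600 mg, 2000 mg and 2000 mg plus flucytosine. Section 9.5.1 calls between-dose comparisons in Stage 1 largely descriptive. This stands: the comparison with 1200 mg rests on objective 1.2.1, and 9.5.2 is touched mainly through Cohort 1B.

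**The grading rule did not change.** The committee invoked a table already in force, and no section says Cohort 1 was under-graded. This also stands. A reader might infer that the Grade 3 rule was tightened; the text supports only an instruction to apply it strictly, from which laxer earlier grading is a possible inference.

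**The ratio rests on assumptions.** Repeated QTc readings in one person are unlikely to be independent, and with perfect correlation a third ECG adds nothing. Deaths and withdrawals before day 28 reduce it too. A greater risk at week 4 than on Days 4 and 7 would raise it. The direction under equal risk survives; the size is not established.

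**This is analysis-plan detail.** The protocol defers detail on secondary endpoints to an analysis plan that is not shown, and recorded QT values allow later regrading. That lowers the priority. But the protocol itself records the change in ascertainment and sets an objective that spans it, without reconciling the two.

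**Conclusion.** The point holds in limited form. Comparisons of Grade 3-4 QTc events, and of QTc-driven interruptions or discontinuations after day 14, between 1200 mg and the higher doses are expected to be biased toward more events at 1600 and 2000 mg. Pooled ampho B QTc rates are slightly affected. Under equal risk and independent ECGs the schedule alone gives a ratio of about 1.4 to 1.5 for assumed per-ECG chances of 2% to 10%, and less with within-person correlation. The conclusion assumes that most Cohort 1 participants did not have the week-4 ECG; some late entrants may have had it.

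Two stronger readings should be resisted. One is that the higher doses must show more QTc events by construction: expected detection rises, but small counts may tie or reverse. The other is that the MTD or the choice between 1600 and 2000 mg is distorted: the added ECG falls outside the DLT window, and both those doses were enrolled after the change. Only the grading instruction could reach DLT, and whether it did is not documented.

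**What to change.** In section 9.5, state that QTc comparisons involving Cohort 1 participants (1200 mg and the concurrent ampho B group) use the Day 4 and Day 7 ECGs common to all cohorts. QTc and its grade should be recomputed for every participant from recorded QT, heart rate and baseline, with both DAIDS Grade 3 criteria applied. Week-4 ECG results should be reported separately for the cohorts that had that ECG.

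The cost is a few sentences and some programming on values that section 6.3.12 already requires to be recorded. The downside is small: week-4 QTc events leave the comparison with 1200 mg, though they are still reported. Regrading aligns event counts but cannot recreate interruptions that a stricter reading at the time might have prompted, so QTc-driven interruptions in Cohort 1 should carry that caveat. No clinical rule changes.
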